## Abstract

**Background:**

This study aims to identify risk factors and the neurodevelopmental impact of neonatal hyperbilirubinemia in a limited-resource setting among a refugee and migrant population residing along the Thai-Myanmar border, an area with a high prevalence of glucose-6-phosphate dehydrogenase-deficiency.

**Methods:**

This is an analytic, observational, prospective birth cohort study including all infants of estimated gestational age equal to or greater than 28 weeks from mothers who followed antenatal care in the Shoklo Malaria Research Unit clinics. At birth, a series of clinical exams and laboratory investigations on cord blood will be carried out. Serum bilirubin will be measured in all infants during their first week of life. All the infants of the cohort will be clinically followed until the age of one year, including monitoring of their neurodevelopment.

**Discussion:**

The strength of this study is the prospective cohort design. It will allow us to collect information about the pregnancy and detect all infants with neonatal hyperbilirubinemia, to observe their clinical response under treatment and to compare their neurodevelopment with infants who did not develop neonatal hyperbilirubinemia. Our study design has some limitations in particular the generalizability of our findings will be limited to infants born after the gestational age of 28 weeks onwards and neurodevelopment to the end of the first year of life.

**Trial registration:**

ClinicalTrials.gov ID NCT02361788, registration date September 1st, 2014.

## Background

Clinically significant neonatal hyperbilirubinemia (NH) is an important cause of neonatal morbidity and mortality and the most frequent reason for delayed hospital discharge or readmission in the first week of life worldwide [1, 2]. Low- and middle-income countries, however, disproportionately bear the burden of severe NH [1, 3] especially countries with a high prevalence of glucose-6-phosphate dehydrogenase (G6PD)-deficiency [4]. In addition to the difficulty of establishing routine G6PD-deficiency screening in newborns as recommended by the World Health Organisation [5] other challenges which impact on NH prevail, including: rhesus sensitization, maternal health-seeking behaviour, availability of neonatal units, and use of guidelines for early recognition and treatment of NH. In developing countries, NH is also one of the main causes of neurodevelopmental impairment in infants, especially in premature infants [1, 3], even though the harmful consequences of NH could be easily prevented by early detection and phototherapy [6, 7].

A recent meta-analysis of NH in low- and middle-income countries highlighted the need for more robust epidemiological studies to identify additional risk factors that may be particular to these settings [3]. In addition, there are no guidelines to prevent and manage NH in low resources settings. Olusanya, et al. have proposed adapting existing guidelines from high level income countries for NH screening in low resource settings [8]. However, as NH is often the result of complex interactions with multiple causes linked to the population and the environment, the development of context-specific guidelines may be more appropriate for these populations particularly affected by NH.

This manuscript summarizes the protocol of an analytic, observational, prospective birth cohort study which will identify local risk factors associated with NH in a limited-resource setting. As far as we are aware this will be the largest birth cohort study that combines research on the risk factors of NH and follow-up monitoring up to one year of life in South East Asia [9–12]. The information gathered from this study will be used to improve and adapt existing guidelines for resource-constrained environments, help develop locally relevant protocols, and make evidence-based recommendations on where and how limited resources can be best allocated to reduce the risks and the negative outcomes of NH. At the time of writing this protocol seven of the eight refugee camps on the Thai-Myanmar border where the study will take place do not have access to point of care G6PD testing, serum bilirubin (SBR) measurement or phototherapy units.

## Methods

### Objectives

The study primary objective is to determine the risk factors associated with moderate and severe NH [6]. The secondary objectives are to: i) determine the incidence of NH and of prolonged jaundice; ii) compare the SBR trend and response to phototherapy by risk factors associated with moderate and severe NH; iii) determine whether severe NH impairs neurodevelopment.

### Setting

The Shoklo Malaria Research Unit (SMRU) is a recognised field research unit working with the refugee (since 1986) and the migrant populations (since 1998) residing on the Thai-Myanmar border [13]. SMRU provides free medical and obstetric care in three clinical sites along the border. All women are invited to the antenatal care (ANC) clinic as soon as they are aware of their pregnancy. During the first ANC visit a dating ultrasound accurately determines the gestational age of the pregnancy. This is important in the context of this study because prematurity is a major risk factor for NH [6]. All women attending ANC are routinely screened for G6PD (fluorescent spot test) and thalassemia, and their ABO group is determined. They are provided with maternity services and are encouraged to deliver at the SMRU clinic although traditionally women birthed at home. Neonates in need of medical attention are admitted to the special-care baby unit (SCBU) and older infants to the inpatient department.

The study will take place in the three SMRU-SCBUs (established between 2008 and 2009) where local medics and nurses work under supervision and receive training by an expatriate doctor. SBR measurement and blue light phototherapy were introduced in 2009 using the US National Institute for Health and Care Excellence Guidelines (NICE) for clinical care of NH [6].

### Study design and patient recruitment

The study will be an analytic, observational, prospective birth cohort study.

All women attending ANC will be provided with information about the study during the 3rd trimester of their pregnancy and provide informed consent for the newborn if they are willing to participate. Maternal demographic, medical and obstetric history will be collected at the time of enrolment. All infants born in an SMRU birthing facility will be included unless born extremely premature (defined in this study and other low resource settings as a gestational age of less than 28 weeks). In this cohort, the incidence of NH will be determined (Fig. 1).

**Fig. 1 Fig1:**
[figure not shown]
Enrolment and eligibility. The figure presents the enrolment eligibility criteria in pregnancy, at birth (for those born in SMRU settings) and in the first week of life (for those born at home or another hospital)

Of the women who attended SMRU ANC, approximately 10% give birth at home and 8% in another hospital. Any infant born outside the SMRU clinic will be eligible if they present in the first 48 h of life, or if they present with jaundice from 48 h to 8 days of life.

The study start-up will be staggered to ensure that each of the teams in the three study clinical sites can operate smoothly and consistently. At each site, the period of enrolment will last one calendar year. The infants will be followed up monthly until they reach twelve months of age. The study recruitment is expected to close on May 13, 2017.

### Study procedures

A timeline of the study procedures is presented in Fig. 2. At birth, umbilical cord blood will be collected. The use of umbilical cord blood allows enough blood volume for several tests including: blood group and Coomb’s test, G6PD testing, albumin level and genotyping of three different loci (G6PD-deficiency, Southeast Asia Ovalocytosis and Gilbert’s syndrome).

**Fig. 2 Fig2:**
[figure not shown]
Study procedure timeline. Timeline of the different clinical and laboratory procedures from birth to 1 year of age. * G6PD deficiency, Southeast Asian Ovalocytosis and Gilbert’s syndrome. Del: Delivery, W: week, M: month

Within the first 24 h a physical examination including anthropometry measurements and clinical jaundice evaluation will be performed as part of routine neonatal care. The mother will be questioned about breastfeeding, use of medicines or preparations for the infant, and the use of naphthalene creams or balls. The NICE Guidelines for clinical care of NH, defining, for each gestational age, SBR measurement and treatment thresholds for moderate and severe NH, will be used in this study to minimize misclassification.

The follow-up schedule will consist of 4 visits in the first week of life, weekly visits until 1 month of age and then monthly visits until 12 months of age (Fig. 2). To ensure adequate attendance to follow-up, each appointment date will be reported in the participant’s medical booklet and parents of the participant who missed an appointment will be called by phone or visited by a health worker. In addition, parents accompanying the child will be compensated for loss of work and travel expenses at an appropriate local rate.

During the visits, routine examination will include anthropometric measurements and physical examination. Laboratory examination will include regular haematocrit (Hct) testing, G6PD testing repeated at 1 month and haemoglobin (Hb) typing at 1 year of age. Quantitative spectrophotometric assay will be carried out in a subsample of females to characterize the enzymatic activity of heterozygous subjects and the associated risk of developing NH.

The infant neurodevelopment will be assessed using the Shoklo Developmental Test at 3, 6, and 12 months [14]. Scoring will be based on a pass/fail system for each item of the test; the global score of the test will be obtained by adding up all the passed scores of the following categories; eye-hand coordination, gross motor, social and speech development. Tone and behaviour during the test will be assessed and scored separately by circling the most appropriate pre-coded diagram (for tone) or description (for behaviour).

### Clinical care

The clinical and research experience of the staff in conjunction with reliable laboratory services and treatment facilities will permit an efficient management of NH. Each SBR measurement will be immediately plotted on a jaundice treatment graph specific for the gestational age (NICE graph) to assess the need for additional follow-up visits, phototherapy, or referral to a tertiary hospital. Infants requiring an exchange transfusion (SBR > 550 μmol/L at any time, with or without clinical signs) will be transferred to the local Thai Hospital in Mae Sot (60 km away). In case of prolonged jaundice (more than 21 days) there will be further investigations [6].

During the neonatal period, weight will be regularly measured and if there is ≥ 10% weight loss compared to the birth-weight the infant will be examined carefully for any underlying causes and necessary care will commence. All medical conditions including anaemia, defined as Hct < 33% will be treated according to standardized guidelines used in this area (Burmese Border Guidelines [15]).

### Outcomes

The primary outcome of this study will be to measure the relative risk of factors associated with moderate and severe NH in infants born at SMRU and to calculate their population-attributable fraction. The secondary outcomes will be to: i) determine the incidence of NH and of prolonged jaundice; ii) measure the changes in the trend of consecutive SBR and the duration of phototherapy according to the risk factors; iiia) compare the clinical condition (anaemia incidence, stunting prevalence) between severe and moderate NH, and normal bilirubinaemia in the first year of life; iiib) compare the neurocognitive developmental, tone and behaviour total scores at one year of life between severe and moderate NH, and normal bilirubinaemia.

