### Sample size

A convenience sample including all births within a one year timeframe at each site was chosen. Based on previous SMRU studies, it is assumed that most mothers will agree to participate in this study and that 15% of infants will be lost to follow-up before completion of the study. More than 90% of women in the area attend ANC. In 2014 more than 80% of women who attended ANC care birthed at SMRU clinics (2040 infants born alive of 28 weeks or more gestational age). It is expected that 1734 infants will be included in the study.

With a total sample size of 1734 infants and an approximate prevalence for NH of 15%, the statistical power (two-sided 95% confidence interval) of a relative difference in the risk of NH of 1.5 fold and 2-fold, in association with a binary risk factor with a prevalence of 10, 20 or 50%, is presented (Table 1).

**Table 1 Tab1:** Statistical power calculations

	Relative risk (RR) for NH associated with binary risk factor	
	RR = 1.5	RR = 2.0
Binary risk factor prevalence	Statistical power	
10%	71%	99%
20%	86%	99%
50%	97%	99%

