### Data collection and analysis

Data will be collected on pre-coded forms and stored in a purpose-designed Microsoft Access database. A hypothesised causal diagram for how factors associated with NH may be connected will be constructed. The incidence of NH and corresponding 95% confidence interval will be calculated within the population of newborns born in the SMRU clinics only; eligible newborns born outside SMRU facilities will be excluded from the incidence analysis as they might falsely increase the incidence of NH in this population. Following this, univariate and multivariate logistic regressions will be performed to identify risk factors for NH. Stepwise logistic regression modelling with backward elimination will be performed on the subset of candidate risk factors selected based on *p*-value < 0.10 in the univariate regression analyses. Key confounders, identified a priori in the causal diagram will be forced into the model. To estimate the association between NH and neurocognitive score, multivariate linear regression will be performed with adjustment for the confounders identified in the causal diagram. Pre-planned subgroup analysis will be conducted in order to identify risk factors associated with moderate and severe NH and estimate the association between NH and neurodevelopment (measured as a continuous neurocognitive score). The description of the clinical course will be supported by SBR measurement tracking recorded on the treatment graph. SBR measurements will be modelled to understand factors impacting on trends [6]. A senior biostatistician will oversee the statistical analyses.

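### Growth is compared between NH groups only as stunting prevalence; adding continuous length-for-age would recover information at almost no cost

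*Protocol article*

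**What the plan says.** The Outcomes section lists, as secondary outcome iiia, to "compare the clinical condition (anaemia incidence, stunting prevalence) between severe and moderate NH, and normal bilirubinaemia in the first year of life". No other growth measure is named there. The Data collection and analysis section describes no growth analysis, binary or continuous.

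The measurements come from the Study procedures section. At birth, "Within the first 24 h a physical examination including anthropometry measurements and clinical jaundice evaluation will be performed". At follow-up, "During the visits, routine examination will include anthropometric measurements and physical examination", on a schedule of "4 visits in the first week of life, weekly visits until 1 month of age and then monthly visits until 12 months of age". The word length does not appear, and the article gives no stunting cut-off, no age at which prevalence is taken and no expected rate.

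The companion neurodevelopment outcome is treated differently. It is "measured as a continuous neurocognitive score" and analysed by linear regression adjusted for the confounders in the causal diagram.

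**The concern.** Stunting keeps one bit per infant: below the cut or not. Two infants just either side of the cut count as different, while two infants far apart on the same side count as the same. No reason for using only the cut is stated.

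This matters most for severe NH, which is some fraction of an assumed 15% NH prevalence and therefore a small group. Enrolment is fixed at one calendar year per site, so numbers cannot be raised to compensate. A real but modest growth deficit would more often go undetected on the prevalence scale, and the resulting interval would be wide.

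**Working it through.** **Inputs from the article (Sample size).** "2040 infants born alive of 28 weeks or more gestational age" and 15% loss to follow-up give 2040 × (1 − 0.15) = 1734, which reproduces "It is expected that 1734 infants will be included in the study". At 15% NH: 0.15 × 1734 ≈ 260 NH infants and 0.85 × 1734 ≈ 1474 normal infants. Two-sided 5% level.

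**Assumptions (not in the article).** Length-for-age is normal; NH shifts the whole distribution down by d SD; stunting in normal infants is 10% to 40%; severe NH is 10%, 20% or 30% of NH, that is 26, 52 or 78 infants.

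**Step 1: information kept by the cut.** Relative efficiency = φ(c)² / [p(1 − p)], with c = Φ⁻¹(p). At p = 0.20: c = −0.842, φ(c) = 0.280, so 0.280² / 0.16 = 0.49.

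| Stunting in normal infants | Kept | Lost |
|---|---|---|
| 5% (outside the main range) | 0.22 | 78% |
| 10% | 0.34 | 66% |
| 20% | 0.49 | 51% |
| 30% | 0.58 | 42% |
| 40% | 0.62 | 38% |

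**Step 2: power, 52 severe v 1474 normal, d = 0.3, 20% stunting.**

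- Continuous: Φ[d / √(1/n₁ + 1/n₀) − 1.96] = Φ[0.3 / 0.1411 − 1.96] = Φ(0.166) = 57%.
- Cut: p₁ = Φ(−0.842 + 0.3) = 29.4%. Pooled proportion = (52 × 0.294 + 1474 × 0.20) / 1526 = 0.203. Standard error is 0.0568 under the null and 0.0640 under the alternative. Power = Φ[(0.0940 − 1.96 × 0.0568) / 0.0640] = Φ(−0.269) = 39%.

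**Step 3: other group sizes, d = 0.3, 1474 normal infants.**

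| Severe infants | Continuous | Cut, 10% stunting | Cut, 20% | Cut, 40% |
|---|---|---|---|---|
| 26 | 33% | 23% | 25% | 24% |
| 52 | 57% | 35% | 39% | 40% |
| 78 | 73% | 44% | 52% | 55% |

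**Step 4: a case that needs no severe share.** All 260 NH v 1474 normal, d = 0.2: 84% continuous v 59% on the cut at 20% stunting. Over 10% to 40% stunting the gap is 18 to 36 percentage points.

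**Step 5: sensitivity to what 1734 means.** The article calls 1734 the number included, although the arithmetic already removes the 15% loss. If 15% of the 1734 were lost as well, 0.85 × 1734 ≈ 1474 infants would remain in total: 44 severe (20% of NH) and 1253 normal. At d = 0.3 and 20% stunting, power is then 50% v 35%. The gap hardly changes.

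**The case against.** Four objections carry weight.

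- **The article is a condensation.** It fixes no growth model or test, and nothing in it rules out a length-for-age analysis in the full protocol or analysis plan. This stands. The point is limited to the outcome as named, which is binary.
- **Prevalence suits the purpose.** Outcome iiia concerns clinical condition and pairs stunting with anaemia, itself defined by a haematocrit below 33% (Clinical care). How many infants are affected is a proper question for a study meant to inform guidelines. This stands, and it is why stunting prevalence should not be demoted or removed.
- **Growth is peripheral.** It is not in the Objectives, and no power is claimed for it. This stands and keeps the point minor.
- **The model favours the continuous scale.** A uniform shift is assumed. If severe NH affects a minority of infants, a measure of the lower tail loses less. This stands, and the figures must carry that caveat.

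A reader might also infer three stronger things that the article does not support. One is that length is recorded at every visit: the text says only that anthropometry is part of the routine examination. Stunting needs length at some age, not at each visit. Another is that half the information is lost as a fact of this study: that figure needs stunting near 20%, which is an assumption. The third is that the different handling of the neurocognitive score is a contradiction: no impairment cut-off is given for that score, so it only shows that a suitable model is already planned.

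**Conclusion.** The point holds as a minor improvement. The only named growth comparison uses a cut of a measure that must already be in hand, and the cut is less efficient in every scenario tabulated. Under a normal shift, the loss is about 38% to 66% of the information over 10% to 40% stunting. At a 0.3 SD deficit, 20% stunting and 26 to 78 severe infants, this costs about 8 to 22 percentage points of power. These sizes rest on an assumed stunting rate, an assumed severe share and the uniform shift.

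It would be wrong to conclude that the continuous scale makes the severe-NH comparison well powered. At 0.3 SD it reaches 33%, 57% and 73% for 26, 52 and 78 severe infants. The gain is in precision.

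**What to change.** Add to secondary outcome iiia a comparison of length-for-age z-score at 12 months, as a continuous outcome, between severe NH, moderate NH and normal infants. Use the confounder-adjusted linear regression that Data collection and analysis already plans for the neurocognitive score, and report mean differences from the normal group with 95% confidence intervals. Use a mixed model over repeated measurements only if length is in fact recorded at several visits. Keep reporting stunting prevalence by group as the clinically interpretable measure.

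The cost is about one sentence of outcome and analysis wording and one extra secondary analysis. No new measurement is needed, provided the length used to classify stunting is available at 12 months. The downside is that a z-score difference is less familiar to public-health readers, which is a further reason to show the prevalence beside it.

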### Sample size

A convenience sample including all births within a one year timeframe at each site was chosen. Based on previous SMRU studies, it is assumed that most mothers will agree to participate in this study and that 15% of infants will be lost to follow-up before completion of the study. More than 90% of women in the area attend ANC. In 2014 more than 80% of women who attended ANC care birthed at SMRU clinics (2040 infants born alive of 28 weeks or more gestational age). It is expected that 1734 infants will be included in the study.

With a total sample size of 1734 infants and an approximate prevalence for NH of 15%, the statistical power (two-sided 95% confidence interval) of a relative difference in the risk of NH of 1.5 fold and 2-fold, in association with a binary risk factor with a prevalence of 10, 20 or 50%, is presented (Table 1).

**Table 1 Tab1:** Statistical power calculations

	Relative risk (RR) for NH associated with binary risk factor	
	RR = 1.5	RR = 2.0
Binary risk factor prevalence	Statistical power	
10%	71%	99%
20%	86%	99%
50%	97%	99%

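### 1734 is the expected 12-month completer count but is used as N for the first-week NH outcome (a conservative error), and the RR = 1.5 column of Table 1 does not follow from its stated inputs

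*Protocol article*

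**What the plan says.** All figures are in the protocol article, Methods, Sample size, unless noted.

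- The base is the 2014 count of SMRU births: "2040 infants born alive of 28 weeks or more gestational age".
- The only quantified loss is that "15% of infants will be lost to follow-up before completion of the study". Under Study design and patient recruitment, follow-up runs to twelve months of age. Consent is described only in words: most mothers are expected to agree.
- The result: "It is expected that 1734 infants will be included in the study".
- Power is then calculated "With a total sample size of 1734 infants" and an "approximate prevalence for NH of 15" per cent, with a "two-sided 95% confidence interval", for a binary risk factor present in 10, 20 or 50% of infants. Table 1 gives 71%, 86% and 97% for RR = 1.5, and 99% in all three cells for RR = 2.0.
- The Abstract (Methods) fixes when the outcome is known: "Serum bilirubin will be measured in all infants during their first week of life".
- Under Outcomes, the primary outcome concerns risk factors for moderate and severe NH in infants born at SMRU.

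**The concern.** There are two separate problems with the planning figures.

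The first is the denominator. An infant lost at eight months has a known first-week NH status and belongs in the risk-factor analysis. Loss over twelve months therefore does not reduce the N for the primary outcome, whereas refusal of consent does, and no rate is given for it. Describing 1734 as the number included also misleads about the later outcomes. If 1734 were really enrolled and 15% were then lost, 1734 x 0.85 = 1474 would remain for the one-year neurodevelopment comparison.

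The second is the table. It is the protocol's only power statement and tells the reader which exposures the study can assess at RR = 1.5. If no single set of inputs gives all three cells, a reader cannot tell which assumptions the column rests on.

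**Working it through.** **Reproducing N.** 2040 x (1 - 0.15) = 1734 exactly. So 1734 is the 2014 birth count less loss by study completion, with no deduction for refusal.

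**Reproducing Table 1.** Stated inputs: N = 1734, NH 15%, two-sided 5%, exposure prevalence e = 0.10, 0.20, 0.50. The section does not say whether 15% is the risk overall or in the unexposed, so both are tried.

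- n1 = eN (exposed), n0 = (1 - e)N (unexposed), p1 = RR x p0.
- Overall reading: p0 = 0.15 / (1 + e(RR - 1)). Unexposed reading: p0 = 0.15.
- pbar = e p1 + (1 - e) p0.
- SE0 = sqrt[pbar(1 - pbar)(1/n1 + 1/n0)].
- SE1 = sqrt[p1(1 - p1)/n1 + p0(1 - p0)/n0].
- Power = Phi[(p1 - p0 - 1.96 SE0) / SE1].

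Example, overall reading, e = 0.10, RR = 1.5: n1 = 173.4, n0 = 1560.6; p0 = 0.15/1.05 = 0.1429, p1 = 0.2143; SE0 = 0.02858, SE1 = 0.03240. Power = Phi[(0.07143 - 0.05602)/0.03240] = Phi(0.476) = 68.3%, against 71% stated.

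Example, unexposed reading, e = 0.20, RR = 1.5: n1 = 346.8, n0 = 1387.2; p0 = 0.15, p1 = 0.225; SE0 = 0.02228, SE1 = 0.02439. Power = Phi[(0.07500 - 0.04367)/0.02439] = Phi(1.284) = 90.1%, against 86% stated.

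| RR = 1.5 | e = 10% | e = 20% | e = 50% |
|---|---|---|---|
| Table 1 | 71 | 86 | 97 |
| N = 1734, 15% overall | 68.3 | 86.7 | 93.9 |
| N = 1734, 15% in unexposed | 70.6 | 90.1 | 98.0 |
| N = 2040, 15% overall | 74.6 | 91.3 | 96.7 |
| N = 2040, 15% in unexposed | 76.8 | 93.9 | 99.2 |

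Under the overall reading the 10% and 50% cells are stated about 3 points too high. Under the unexposed reading the 20% cell is stated 4 points too low and the other two fit within a point.

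**Other tests at N = 1734.** Unpooled variance gives 59.7/82.6/94.0 (overall) and 62.3/86.8/98.0 (unexposed). Continuity correction gives 64.7/85.0/93.0 and 67.2/88.7/97.7. Log-RR, log-OR, arcsine and exact versions also fail to bring all three cells within 2 points.

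**Could another N explain it?** Not for the pooled test, allowing 2 points either way. Under the unexposed reading the 10% cell needs N between 1665 and 1845, and the 20% cell between 1422 and 1613. Under the overall reading the 20% cell needs 1597 to 1811, and the 50% cell 1835 to 2588. Neither pair overlaps.

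**RR = 2.0 at N = 1734.** The first cell is 98.9% (overall) or 99.5% (unexposed), and the other cells exceed 99.9%. The stated 99% is right to within about a point.

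**The case against.** The best defence is that nothing turns on these numbers. The sample is a convenience sample of all births in a calendar year at each site, so power is descriptive and sets no enrolment target. The 15% is itself approximate: under the overall reading, moving it from 14% to 16% shifts the 10% cell from 65.1% to 71.3%, as much as the misses found here. All of this stands, and it limits the weight of the point. It does not make the column follow from its inputs.

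A reader might go further and infer any of the following, which the document does not support.

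- *That Table 1 overstates power.* This holds only if 15% is the overall risk and N is 1734. With 15% in the unexposed, no cell is more than half a point too high. With N = 2040 and 15% overall, the computed 74.6/91.3/96.7% meets or exceeds the stated column after rounding. The smaller N offsets the apparent excess.
- *That the cells were computed under different conventions.* The 71% fits one reading and the 86% the other, but the document does not show how they were obtained.
- *That infants born outside SMRU were wrongly left out of N.* The primary outcome is restricted to SMRU-born infants, so leaving them out is consistent.
- *That the first-week N should be 2040.* That is an upper limit at full consent. A consent rate of 85% would happen to give 1734, but the 15% in the text is loss to follow-up, not refusal.

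**Conclusion.** Both parts hold as errors in the stated planning figures, and both are modest.

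1734 is the expected number of 12-month completers from 2040 births. It is mislabelled as the number included and misapplied as N for an outcome known in the first week. At full consent, using 2040 instead adds about 1 to 6 points of power at RR = 1.5, so the error is conservative. As a completer count for the one-year outcomes, 1734 is reasonable if consent is close to complete.

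The RR = 1.5 column is not reproducible at the stated N and two-sided 5% level under one meaning of the 15%. The largest miss with the pooled test is about 3 points (overall reading) or 4 points (unexposed reading), in opposite directions. Since the protocol does not say which meaning applies, no direction of bias can be assigned. The RR = 2.0 column and the study's feasibility are unaffected.

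**What to change.** In the Sample size section:

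1. Give two numbers: the infants expected in the first-week NH analysis (2040 x an explicit consent rate, SMRU-born), and the infants expected at 12 months (that number x 0.85).
2. Say whether 15% is the NH risk overall or in the unexposed, and name the test behind the power figures.
3. Recompute the RR = 1.5 column on the first-week N under that one convention. With full consent and a pooled two-proportion test it would read 75/91/97% if 15% is the overall risk, or 77/94/99% if it is the unexposed risk. A lower consent rate reduces these figures.

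The cost is a few restated figures and one recalculation. Enrolment, procedures and follow-up do not change.
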